### Recruitment {15}

Our target population is Kenyan adolescents aged 13 to 20 years who are currently in high school. We aim to recruit 25 schools with a mix of boarding, day, girls-only, boys-only, and mixed-gender schools. The schools we target will be either county, extra-county, or sub-county schools. Heads of the targeted schools will be contacted and informed about the study, after which they will be asked to sign a Memorandum of Understanding (MoU) and provide a contact person from the school to work with us. From the list of schools that sign up for the program, we will select seven schools to create a sub-sample of 1600 students. This will take into consideration the classification of the school (i.e., county, extra county, boy-only etc.), the school population, the school location, and other logistical considerations (e.g., ensuring there are enough lay providers to facilitate sessions on the days proposed by schools). We will include a certain number of students from each school in the sample to ensure that we have 1600 students in total, with an equal gender split. Those in the selected sample schools who are not included in the sample will receive intervention, however will not complete any data collection measures.

## Assignment of interventions: allocation

### Sequence generation {16a}

Consenting students will be randomized into one of the three intervention arms using “ballot boxes.” Each supervisor will prepare a “ballot box” containing small pieces of paper which will indicate the group numbers and the intervention arm assigned. Participants will be invited to line up and pick a folded piece of paper from inside the ballot box, which will indicate their group number and allocated intervention. We aim to have equal numbers of students in each randomized group.

### Concealment mechanism {16b}

The numbers inside the ballot boxes will be folded and thus concealed when the participant picks their number, preventing them from influencing their group assignment. This approach guarantees an equal chance for each participant to be placed in any of the groups.

### Implementation {16c}

Once students have been given their group numbers, they will go to their assigned groups to meet their group leaders, who will then confirm that they are in the correct group. Once the participant’s settle in their groups, the group leader will direct the filling of an attendance sheet containing participant information—name, admission number, and form—then randomization will be complete. The specific groups and arms assigned will be maintained throughout the study.

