### Who will take informed consent? {26a}

Local customs and policies authorize school administrations to decide on any activity (including research) involving students. Therefore, the school heads will represent guardians and parents in receiving information about the study and may contact parents and guardians according to local customs [22]. The school heads will be given the opportunity to ask questions concerning the study and provide consent for all students by enrolling their school into the program by signing an MoU. The school administrators will be given an option to contact the students’ parents and guardians at home if they deem it appropriate.

Also, before sessions begin, interested students will be provided with more information about the study and an opportunity to ask questions. Students will be informed that participating in the study is voluntary and that they can opt out of the study at any time. Interested students will then be asked to provide consent, or assent for minors, prior to enrollment in the study.

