## Statistical methods

### Statistical methods for primary and secondary outcomes {20a}

Our data analysis plan will involve descriptive statistics, visualizations, and models of change over time. We will follow an intent-to-treat approach [41], analyzing all the study participants assigned to their intervention arm. Our findings will be summarized using tables and graphs.

For descriptive statistics, we will compute the frequencies and percentages of the demographic and clinical characteristics for the study participants at baseline by the intervention arm. To test for significant group differences in the sample characteristic variables, we will use *F*, *t*, and *χ*^2^ statistics [42].

Primary outcome variations across all the time points will be visualized using multiple plots. We will include line plots for depressive symptoms, anxiety symptoms, academic grades, well-being, and perceived social support for the Shamiri intervention per implementer and TAU control arm, visualizing scores before, during, and after the intervention and control condition.

We will build linear mixed effects models [43, 44] as part of the analysis to compare the outcomes of the two Shamiri intervention and the TAU control groups. These models will consider the hierarchical nature of the data, where participants are nested within organizational structures (participant in lay provider/group in school in county). The standard models will be random-intercept models; we will also test the inclusion of random slopes for individual differences. Some of the model elements (e.g., multiple levels of nesting and the random slope) may result in models that are too complex, unidentifiable, or overfit; in such a case, more parsimonious models will be selected.

The arm, time, and interaction between these two will be included in all the models as fixed effects. Other variables that will be included either in a fixed effect or in a random effect specification in the models are age, gender, lay provider, lay provider gender, school, and county. Baseline scores may also be included. Age will be included as a covariate as older adolescents in Kenya have been found to on average have increased psychosocial stress compared to younger adolescents which may heighten depressive and anxiety symptoms [12].

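### Randomisation is declared complete only at an attendance sheet filled after the arm is known, and the article does not say whether the draw or the sheet defines the intent-to-treat set

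*Protocol article*

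**What the plan says.** Sequence generation {16a} has consenting students line up and "pick a folded piece of paper from inside the ballot box, which will indicate their group number and allocated intervention". Concealment mechanism {16b} describes the slip as "concealed when the participant picks their number, preventing them from influencing their group assignment"; it says nothing about the interval after the slip is opened.

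Implementation {16c} gives the next steps. Once students have their numbers, "they will go to their assigned groups to meet their group leaders, who will then confirm that they are in the correct group". After they settle, "the group leader will direct the filling of an attendance sheet containing participant information", and "then randomization will be complete". The fields listed for the sheet are name, admission number and form.

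Who will be blinded {17a} states that students, lay providers and supervisors cannot be blinded to allocation. Statistical methods {20a} describes intent-to-treat as "analyzing all the study participants assigned to their intervention arm". On consent, section {26a} says: "Interested students will then be asked to provide consent, or assent for minors, prior to enrollment in the study".

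**The concern.** Concealment protects a comparison only if nobody can act on the allocation between learning it and having it recorded. Here the student learns the arm at the box, and the first described record tying a name to an arm is made later, inside the group, directed by a leader who also knows the arm. In that interval a student can leave, or trade slips with a friend, and nothing described in the article would preserve the arm drawn.

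The article also offers two candidate points of randomisation. Sections {16a} and {16c} speak of the intervention as allocated and the group as assigned from the draw, while {16c} also says randomisation is complete only after the sheet. The choice affects who is in the analysis set:

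- If the draw counts, intent-to-treat needs a record of the draw, and none is described.
- If the sheet counts, a student who left after seeing the slip was never randomised and falls outside the set by definition.

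At stake is selection made with knowledge of the arm. It could bias comparisons with treatment as usual (TAU) and between the two delivery arms.

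**Working it through.** No figure in the article is in dispute. The check has two parts.

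**Order of events, set side by side**

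1. Consent or assent ({26a}) comes before enrolment, so a consent record may exist, but it carries no arm.
2. The draw ({16a}) reveals group and arm to the student. No name is described as being written against the slip.
3. Concealment ({16b}) is claimed only up to the pick.
4. On arrival ({16c}) the leader confirms the group. If this means reading the slip, it finds a student sitting in a group other than the one drawn. It cannot find exchanged slips, because nothing ties a slip to a name, and it cannot find a student who never arrives.
5. The attendance sheet ({16c}) is the first described link between student and group. Slip number is not among its listed fields; the arm follows from whose sheet it is.
6. Intent-to-treat ({20a}) refers to assignment without naming step 2 or step 5.

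**Possible size, on assumed inputs**

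From the article: target effect 0.22 SD (Sample size {14}). Assumed: a fraction p of one arm leaves unrecorded, and leavers differ from stayers by d = 0.5 SD. The article gives neither p nor d.

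The full arm mean is (1 − p) × stayers + p × leavers, so the recorded mean (stayers only) differs from it by p × d:

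| p | shift (SD) | share of 0.22 |
|---|---|---|
| 0.02 | 0.02 × 0.5 = 0.010 | 5% |
| 0.05 | 0.05 × 0.5 = 0.025 | 11% |
| 0.10 | 0.10 × 0.5 = 0.050 | 23% |

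The contrast between arms moves by this amount only if the comparator has no similar loss.

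Exchanged slips work differently, because each swap moves both means. If a fraction f of each of two arms trade, and the two sets of swappers differ by g = 0.5 SD, the contrast shifts by 2 × f × g. That gives 0.01 SD at f = 0.01, 0.05 SD at f = 0.05 and 0.10 SD at f = 0.10, or 5%, 23% and 45% of 0.22. Again f and g are assumed.

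**Which analysis is affected**

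The first test in {20a} is the arm-by-time interaction. A level difference that stays constant from baseline onward largely cancels there, so the shares above overstate the effect on that test. They apply more directly to the arm differences at single time points, to Cohen's d, and to the main effect used if the interaction is not significant. Including baseline scores, which {20a} leaves optional, would reduce the effect. A difference in how leavers or swappers would have changed over time would not cancel.

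**The case against.** The strongest reply is that the article never says the analysis set comes from the attendance sheet. Its intent-to-treat statement rests on assignment, and both {16a} and {16c} place assignment at the draw. A reader might infer that leavers and swappers do drop out of, or change arm in, the intent-to-treat set. The text does not support that: it leaves the defining point open, and the risk is conditional.

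A second reply is that this is a condensed article. The full protocol is promised online ({31c}), and the partner receives a detailed procedures manual ({18a}), so a draw log may exist. That stands as far as it goes: the lack of a described log does not show that none was kept. It does not dispose of the sentence in {16c}, which is a positive statement of when randomisation ends. If a log exists, that sentence is misleading.

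Third, the leader's check is a real safeguard. It should catch anyone who joins a group other than the one on the slip, leaving early leavers and exchanged slips.

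A reader might also infer that losses would be one-sided, because TAU students receive only their school's usual care, or because Recruitment {15} says students outside the sample still receive the intervention. This is conjecture. No rate is given for any arm, students are told only that different programs are being tested ({17a}), and nothing says a student who leaves would be treated as outside the sample.

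**Conclusion.** The point holds as a weakness in procedure and an ambiguity in definition. Randomisation is declared complete after the arm is revealed, at a record made in the group under an unblinded leader, and {20a} does not say whether the draw or the sheet defines the intent-to-treat set. Post-allocation selection is possible and, on the described procedure, partly undetectable. It has not been shown to have happened.

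Its size is unknown. On the assumptions above, movement by 1% or 2% of an arm would matter little, while selective movement by 5% to 10% could amount to a noticeable share of the 0.22 target. The concern merits correction; it does not invalidate the trial.

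**What to change.** Record admission number, slip number and arm at the box, in draw order, before the student leaves it, preferably by someone outside the arms. State that randomisation is complete at that entry. Define the intent-to-treat set as all logged draws, analysed by drawn arm. Reconcile attendance sheets against the log and report no-shows and swaps by arm.

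The cost is one log sheet per school and a few seconds per student, at an event the supervisors already prepare. The draw becomes slightly slower, and some logged students will have no baseline data.

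Trial status records recruitment as completed on July 14, 2023, so for this trial the remedy depends on what was kept. If a draw log exists, say so and define the set from it. If not, compare the slips issued with the students recorded, by arm, and report the discrepancy and the unrecorded draw as a limitation. That comparison can reveal net losses by arm, but it cannot recover exchanged slips.

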## Assignment of interventions: blinding

### Who will be blinded {17a}

Study participants, lay providers, and supervisors cannot be blinded to treatment allocation; however, they will not be informed about the study objectives. They will only be informed that the study is out to test different programs to better understand their impact on academic scores and wellbeing.

Additionally, the school administrators will not know the participants’ response to any of the questions and the participants will be assured at the beginning of the sessions that their responses will be kept confidential.

### Procedure for unblinding if needed {17b}

Unblinding will only be needed in the event of a safety concern. In such situations, the team responsible for direct implementation (that is, the lay provider, supervisor, and clinical expert) will need to know the participant’s identity and assigned group. Unblinding procedures will only be required for the people interacting directly with the participants in case an emergency case comes up.

## Data collection and management

### Plans for assessment and collection of outcomes {18a}

One member of the study team will lead the production, distribution, collection, and entry of study questionnaires. Centralizing this process will allow quick identification and resolution of issues. The questionnaire will contain the tools mentioned in the “Outcomes {12}” section.

To ensure data quality, we will thoroughly train relevant actors on data handling procedures—we expect the lay providers to guide students as needed while filling the questionnaires. Members of the study team will be present and accessible virtually during the entire process of data collection, and supervisors onsite will assess lay-providers adherence to protocol. We will provide our implementation partner with a detailed manual on all procedures involved— they will be responsible for their entire process of data collection at their assigned sites to provide an accurate picture of the dynamics involved in decentralization.

### Plans to promote participant retention and complete follow-up {18b}

In the participating schools, the study team will meet all the students and hold a presentation about the program during a pre-session 1 week before implementation begins. One teacher will work closely with the study team as the contact person. We will collaborate to create schedules consistent with the schools’ calendars and we will continuously communicate with teachers during the implementation and at follow-up.

Also, we will consistently monitor attendance rates and audio recordings from the weekly sessions. The supervisors will receive attendance data from the lay providers after every session and feed the data into our real time dashboard. The study team will continuously monitor the session attendance and strategize better to promote participant retention throughout the study.

### Data management {19}

We will collect the questionnaires, attendance sheets, and recorders from each lay provider and ensure that they are stored in a safe and enclosed location. The physical questionnaires will be stored in a container and locked. This container will be transported to the coordination site headquarters, for data processing.

We will extract data from the paper questionnaires using *PaperSurvey* and store it in a password-protected database on *Airtable.**PaperSurvey* is an online service that transforms handwritten surveys into digital data with AI recognition technologies while *Airtable* is a cloud-based spreadsheet-database hybrid.

### Confidentiality {27}

We will assign random ID numbers to protect the students’ identities. The questionnaires will be entered in a private setting, kept in a locked cabinet, and destroyed after we have extracted all the data. Only the study team will have access to these materials. No information that may reveal the participants’ identity will be released or published without their consent.

### Plans for collection, laboratory evaluation, and storage of biological specimens for genetic or molecular analysis in this trial/future use {33}

N/A. We will not collect any biological specimens.

## Statistical methods

### Statistical methods for primary and secondary outcomes {20a}

Our data analysis plan will involve descriptive statistics, visualizations, and models of change over time. We will follow an intent-to-treat approach [41], analyzing all the study participants assigned to their intervention arm. Our findings will be summarized using tables and graphs.

For descriptive statistics, we will compute the frequencies and percentages of the demographic and clinical characteristics for the study participants at baseline by the intervention arm. To test for significant group differences in the sample characteristic variables, we will use *F*, *t*, and *χ*^2^ statistics [42].

Primary outcome variations across all the time points will be visualized using multiple plots. We will include line plots for depressive symptoms, anxiety symptoms, academic grades, well-being, and perceived social support for the Shamiri intervention per implementer and TAU control arm, visualizing scores before, during, and after the intervention and control condition.

We will build linear mixed effects models [43, 44] as part of the analysis to compare the outcomes of the two Shamiri intervention and the TAU control groups. These models will consider the hierarchical nature of the data, where participants are nested within organizational structures (participant in lay provider/group in school in county). The standard models will be random-intercept models; we will also test the inclusion of random slopes for individual differences. Some of the model elements (e.g., multiple levels of nesting and the random slope) may result in models that are too complex, unidentifiable, or overfit; in such a case, more parsimonious models will be selected.

The arm, time, and interaction between these two will be included in all the models as fixed effects. Other variables that will be included either in a fixed effect or in a random effect specification in the models are age, gender, lay provider, lay provider gender, school, and county. Baseline scores may also be included. Age will be included as a covariate as older adolescents in Kenya have been found to on average have increased psychosocial stress compared to younger adolescents which may heighten depressive and anxiety symptoms [12].

Gender will be included because Kenyan adolescents have shown gender differences in internalizing problems [8, 12]. Female adolescents have previously reported higher anxiety and depression symptoms as compared to males. Past studies [8, 12] have shown that adolescents in lower-resource schools report higher depression and anxiety symptoms. Lastly, we will include details of lay providers like gender because we would like to explore if the gender of a lay provider affects the study participants.

A *p*-value less than 0.05 in the interaction between the time variable and the arm variable will be considered statistically significant. If the interaction is significant, we will look at the conditional mean difference between the arms at each time point from end point to follow-up. We will assess this and report marginal (predictive) means. If these differences are significant (*p* < 0.05) and the control has scores associated with less favorable outcomes, we will conclude there was improvement due to centralized or decentralized arm over time. If the interaction is not significant but the main effect of centralized or decentralized arm is, and the effect points to lower symptoms in the centralized or decentralized arms, we conclude there was improvement due to centralized or decentralized delivery.

Effect sizes (ESs) will be computed from the mean differences across the different time points for the arms. We will compare Cohen’s D for each outcome at baseline, midpoint, endpoint, and 1-month follow-up for the study participants in the Shamiri intervention arms and TAU control arm. Statistically significant Cohen’s *D* in the direction of less symptoms on average in the arms will reflect greater improvements for intervention compared to control.

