The initial randomized controlled trial of the Shamiri intervention was implemented among school-going Kenyan youths with elevated depression and anxiety symptoms (*n* = 51). Compared to an active study skills control group, the intervention significantly improved participants’ depressive and anxiety symptoms, perceived social support, and academic performance [12]. These findings were replicated in a pre-registered study with a larger sample of participants (*n* = 413) with the intervention’s effects persisting at the 7-month follow-up [8]. The development and evaluation of the Shamiri intervention demonstrate the potential for character strength interventions to improve the mental health, academic, and social outcomes of Kenyan youth.

A question that emerges is how do we scale up these types of interventions to address the youth mental health treatment gap? One way of doing this is developing strategies that can allow for these light-touch, school-based interventions, like the Shamiri intervention, to be delivered through possibly scalable models. Our team sought to develop such a model for the delivery and scaling of the Shamiri intervention. The model that we developed was a three-tier caregiving model consisting of mental health workers with varying levels of training [17]. At the first tier of the model are lay providers; recent high school graduates who receive training to lead group sessions. The second tier consists of clinical supervisors who have some mental health experience (e.g., a bachelor’s degree in psychology) and are further trained through a 7-week program that covers topics including supervision and support for lay providers, handling clinical emergencies, providing one-on-one support to students, and referring participants to the third (expert) tier of the model when necessary. The third tier is composed of a clinical network of Kenyan mental health experts, most with doctoral degrees in psychology or psychiatry [12, 17]. This model, which is sometimes referred to as the “Anansi” model, allows for the expansion of the caregiving supply by mobilizing an expanded array of caregivers and offers opportunities for clinical escalation and triaging [18]. Over the past 3 years, more than 9500 youths have received the Shamiri intervention through the Anansi model, demonstrating the model’s scalability [19, 20].

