### Strategies to improve adherence to interventions {11c}

We will employ several strategies to encourage and evaluate compliance with intervention procedures. The first involves comprehensive training for all lay providers. They will undergo didactic training and engage in roleplays to effectively administer the intervention. They will also be instructed on the use of the emergency protocols when necessary and will be instructed in and expected to follow general trial guidelines, such as maintaining participant confidentiality. This training will be supplemented by tailored assessments such as a post-training readiness survey and real-time role play evaluation and feedback.

Second, we will ensure adherence through supervision. This will include both weekly in-person meetings and daily supervision by trained supervisors to verify compliance with the intervention protocols. All supervisors will have at least a bachelor’s degree in psychology and prior counseling experience. They will undertake a seven-week training on ethical considerations, the Shamiri Intervention, and trial protocols. Furthermore, a clinical network consisting of PhD-level mental health experts will oversee these supervisors.

The final approach is the measurement of adherence to the protocols during intervention implementation. This will be accomplished by enlisting independent raters to assess a randomly selected portion (10%) of session recordings on fidelity and performance, using a method similar to previous trials [8, 13, 20]. Each recording will be evaluated by two independent raters, after training on the use of the fidelity rubric, and their level of agreement will be assessed using Gwet’s AC2 [28, 29] for ordinal rating scales.

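### The stated model hierarchy omits the supervisor tier, so the centralised-versus-decentralised standard error will be too small if supervisors serve one implementer, oversee several groups and differ in effect

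*Protocol article*

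**What the plan says.** Section {20a} describes linear mixed models in which "participants are nested within organizational structures (participant in lay provider/group in school in county". Further terms, fixed or random, are "age, gender, lay provider, lay provider gender, school, and county". Neither list contains the supervisor. The random slopes mentioned are for individual differences, not for school by arm. If the model proves too complex, "in such a case, more parsimonious models will be selected", so the stated flexibility runs only towards fewer levels.

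Elsewhere supervisors are part of the treatment:

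- Background {6a}: "The second tier consists of clinical supervisors who have some mental health experience". Their training covers "supervision and support for lay providers, handling clinical emergencies, providing one-on-one support to students".
- Adherence {11c}: "weekly in-person meetings and daily supervision by trained supervisors to verify compliance with the intervention protocols".
- Non-adherence and missing data {20c}: the supervisor alerts lay providers who deviate and sends them back to the manual.
- Sequence generation {16a}: each supervisor prepares a ballot box with "small pieces of paper which will indicate the group numbers and the intervention arm assigned", which implies several groups per supervisor.

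Trial design {8} randomises students to three arms in seven schools. The section on the choice of comparators {6b} makes centralised versus decentralised delivery the primary objective, and Objectives {7} expects the two to be equally effective.

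**The concern.** Groups that share a supervisor plausibly share delivery quality, so they are not independent given the levels in the model. If students in one school are randomised to both implementers, the school intercept is common to both arms and cancels from their difference. A supervisor who works for one implementer then acts like a school-by-arm effect, and no listed term represents that. The group intercept takes up some of this variance, but the model then averages it over the number of groups and not over the smaller number of supervisors.

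At stake is the comparison that the protocol calls primary. A few weak supervisors could look like a failure of decentralisation, or equal effectiveness could be claimed with more precision than the data hold. Each active arm against treatment as usual would be affected less, because the supervisor variance would enter from one side only. That effect is not quantified here.

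**Working it through.** **Plan's own figure.** There is none for this contrast. The 1554 participants in Sample size {14} were derived for intervention against control, so they are no check on this point.

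**Inputs from the protocol.** 1600 students in three equal arms: 1600/3 = 533 per arm. Groups of 10 to 15, midpoint 12.5: 533/12.5 = about 43 groups per arm (range 36 to 53). Attrition of 40% by follow-up: 533 × 0.60 = 320 completers per arm. Seven schools.

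**Assumptions, not in the protocol.** Total variance 1; group variance v_g = 0.02; supervisor variance v_s from 0 to 0.05; S = 4, 7 or 14 supervisors per implementer; both implementers in every school; two-sided 5% test at one post-baseline visit. Residual v_e = 1 − v_s − v_g.

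**Closed form.** With G groups and n completers per arm:

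- True SE = √[2(v_s/S + v_g/G + v_e/n)]
- Model SE, supervisor variance absorbed by the group term = √[2((v_s + v_g)/G + v_e/n)]
- Actual type I error = 2[1 − Φ(1.96 × model SE / true SE)]

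Example with S = 7 and v_s = 0.02:

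- True SE = √[2(0.02/7 + 0.02/43 + 0.96/320)] = 0.1124
- Model SE = √[2(0.04/43 + 0.96/320)] = 0.0887
- Ratio 1.27; 1.96/1.27 = 1.55; type I error = 0.122

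True SE / model SE, with type I error in brackets:

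| Supervisor ICC | S = 4 | S = 7 | S = 14 |
|---|---|---|---|
| 0 | 1.00 (0.050) | 1.00 (0.050) | 1.00 (0.050) |
| 0.005 | 1.15 (0.087) | 1.08 (0.069) | 1.03 (0.058) |
| 0.01 | 1.27 (0.122) | 1.15 (0.088) | 1.06 (0.065) |
| 0.02 | 1.47 (0.182) | 1.27 (0.122) | 1.12 (0.079) |
| 0.05 | 1.87 (0.295) | 1.52 (0.198) | 1.24 (0.113) |

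The result changes little with a larger remaining group ICC. With v_s = 0.02, v_g = 0.03, S = 7, 42 groups and 315 completers, the true SE is √[2(0.02/7 + 0.03/42 + 0.95/315)] = 0.115. The model SE is √[2(0.05/42 + 0.95/315)] = 0.092, and the type I error is again about 12%.

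**Simulation with fitted models.** REML, 400 runs per setting, 7 schools, 6 groups per school and implementer, 8 completers per group, group variance 0.02, school variance 0.03, normal critical value. Type I error:

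| Supervisor ICC | One per school and implementer, omitted | Same, fitted | Two per school and implementer, omitted |
|---|---|---|---|
| 0 | 0.058 | 0.042 | 0.058 |
| 0.01 | 0.098 | 0.042 | 0.072 |
| 0.02 | 0.128 | 0.055 | 0.052 |
| 0.05 | 0.280 | 0.095 | 0.118 |

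Monte Carlo error is about 0.01 to 0.02. With one supervisor per school and implementer, ICC 0.02 and the term omitted, the mean model SE was 0.084 against an empirical SD of 0.109. The simulation broadly agrees with the closed form. At ICC 0.05 with one supervisor it is worse (0.280 against 0.198), mainly because the fitted model SE was smaller there (0.087 against 0.095), as the school term can take up part of the supervisor variance.

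**The case against.** A reader might infer that the implementer contrast certainly has standard errors that are too small. The protocol does not support that. It gives no number of supervisors, no ratio of groups to supervisors and no supervisor ICC, and it does not say that a supervisor serves only one implementer. The ballot-box wording could even mean that one supervisor's box spans several arms, though it concerns the preparation of the draw and not who supervises delivery. Section {18a} speaks of sites allotted to the partner. If each site had one implementer and one supervisor, the school intercept would already absorb the supervisor. That reading sits badly with individual randomisation to three arms, but it is not excluded. This part of the objection stands and makes the point conditional.

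The size also depends on the layout. With two supervisors per school and implementer, simulated error stayed near nominal up to ICC 0.02. Lay providers lead the sessions and both implementers follow one manual, so the supervisor share may be small. This stands too.

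The calculation uses one post-baseline visit, whereas section {20a} judges an arm-by-time interaction and words its decision rules against control. The error rates above therefore show how far the implementer interval can be trusted; they do not describe a decision rule in the plan.

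Two further arguments carry less weight. One may say that inference is about these two organisations as staffed, so supervisors need not be random. The stated aim, however, is to learn about strategies for scaling up, which reaches beyond the supervisors who happened to be hired. One may also leave the level to a statistical analysis plan. But the protocol does not leave the hierarchy open: it lists the levels, omits this one and allows only simplification.

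**Conclusion.** The omission is plain in the text, and its direction is clear: any positive supervisor variance within implementer, with several groups per supervisor and both implementers in the same schools, makes the standard error of the centralised-versus-decentralised contrast too small. Those conditions are a reasonable inference from the tiered model, from the definition of decentralised delivery as replication by a third party, and from parallel implementation. They are not stated facts.

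On the assumptions above, the harm is nil at ICC 0 and modest with 14 supervisors per implementer (about 6-8% at ICC 0.005-0.02). With 7 it is material (about 9-12% at ICC 0.01-0.02), and it is larger with fewer supervisors or a higher ICC.

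**What to change.** - State how many supervisors each implementer uses, how many groups each oversees and whether any works across arms. Record the supervisor ID for each group.
- In section {20a}, add a random intercept for supervisor within implementer, or a school-by-arm random effect if each school has one supervisor per implementer. Let it act on the post-baseline scores, because an intercept that also spans baseline cancels from change over time.
- Use small-sample degrees of freedom. With a normal critical value, even the fitted supervisor model gave 0.095 at ICC 0.05.
- Drop the term only if its variance is estimated as zero. If it cannot be fitted, give the implementer contrast from the seven within-school arm differences (6 degrees of freedom) as a sensitivity analysis.

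The work is one ID variable and one model term. The price is precision. In the example with 7 supervisors and ICC 0.02, the 95% half-width goes from 1.96 × 0.0887 = 0.17 SD to 2.447 × 0.1124 = 0.28 SD on 6 degrees of freedom. If supervisors do differ that much, the wider interval is the correct one.
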